### Provisions for post-trial care {30}

N/a—After informed consent for the screening has been obtained until the last follow-up visit, all adverse events causally related to a study intervention will be reported according to the regulation of the Ethics Committee Research UZ/KU Leuven. Although adverse events and possible injuries are not expected due to the clinical nature of the study, participants are insured during their participation in all study-related interventions, including the assessments and therapy sessions, through the insurance taken by KU Leuven.

### Outcomes {12}

For the primary outcome and secondary outcomes, an overview of the specific outcome measures, analysis metrics, methods of aggregation, and timepoints of interest is shown in Table 1. Additional information regarding the outcome measures can be found under SPIRIT-item {18a}.

**Table 1 Tab1:** Schematic overview of the specific outcome measures, analysis metrics, methods of aggregation and timepoints of interest for the primary outcome and secondary outcomes

		**Specific outcome measure**	**Analysis metric**	**Method of aggregation**	**Timepoints of interest**
**Primary outcome**					
	**Bimanual performance**	*(Adolescent) Assisting Hand Assessment (AHA/Ad-AHA)*	Change over time	Logit-based total score (0–100)	*T*_0_, *T*_2_
**Secondary outcomes**					
**Motor function**	**Bimanual performance**	*(Adolescent) Assisting Hand Assessment (AHA/Ad-AHA)*	Change over time	Logit-based total score (0–100)	*T*_0_, *T*_1_
		*Children’s Hand-use Experience Questionnaire (CHEQ)*		Logit-based total scores (0–100)	*T*_0_, *T*_1_, *T*_2_
	**Bimanual coordination**	*Kinarm exoskeleton: Ball-on-bar task*		Mean scores per level	
	**Bimanual coordination**	*Box opening task*		Mean scores over 5 trials	
	**Unimanual function**	*Tyneside pegboard test (TPT)*		Completion time in seconds	
	**Goal attainment**	*Goal Attainment Scaling (GAS)*		Classification based on criterion references into 6 categories (− 3–2)	
**Somatosensory function**	**Tactile registration**	*Semmes–Weinstein Monofilaments*		Classification based on threshold values into 5 categories (1–5)	
	**Tactile perception**	*Stereognosis assessment*		Number of correctly identified objects (0–6)	
		*Aesthesiometer*		Minimal distance in mm that can be correctly discriminated 5 consecutive times (3– > 10 mm)	
		*Tactile Discrimination Test*		Area under the curve (0–100)	
	**Proprioception**	*Movement sense*		Classification based on performance into 3 categories (0–2)	
		*Kinarm exoskeleton: Contralateral position matching task*		Mean scores across 24 trials	
		*Kinarm exoskeleton: Perceptual boundary task*		Slope and inflection point of the psychometric curve	
		*Kinarm exoskeleton: Indicating location task*		Number of correctly identified locations (0–12)	
		*ETH MIKE: Passive position sense task*		Mean absolute error across 11 trials	

*Abbreviations:*
*mm* millimeters, *Baseline (T*_*0*_
*)* maximally 2 weeks before the start of the therapy, *Post (T*_*1*_
*)* maximally 2 weeks after the therapy has ended, *Follow-up (T*_*2*_
*)* 6 months after the therapy has ended, within a time frame of 2

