**Table Taba:** 

Title {1}	Does somatosensory discrimination therapy alter sensorimotor upper limb function differently compared to motor therapy in children and adolescents with unilateral cerebral palsy: study protocol for a randomized controlled trial
Trial registration {2a and 2b}.	Primary registry and trial identifying number: ClinicalTrials.gov, NCT06006065 Date of registration in primary register: August 8, 2023 Secondary identifying numbers: G0C4919N, S67467 Source(s) of monetary or material support: The Flemish Research Foundation provides financial support for this study (FWO project, G0C4919N; FWO-fellowship [name], 11PP224N). Primary sponsor: KU Leuven Contact for public queries: [name]; [name]; [contact] ; [name] Contact for scientific queries: PI: [name], Scientific contact delegate: [name]; [name]; [contact] ; [name] Public title: The effectiveness of an intensive therapy program for the upper limb in children and adolescents with unilateral cerebral palsy Scientific title: The effectiveness of an intensive upper limb therapy program focused on somatosensation in children and adolescents with unilateral cerebral palsy Countries of recruitment: Belgium Health condition(s) or problem(s) studied: Unilateral cerebral palsy Intervention(s): Intervention: Upper limb somatosensory discrimination therapy (18 hours over 8 weeks); Active comparator: Upper limb motor therapy (18 hours over 8 weeks) Key inclusion and exclusion criteria: Ages eligible for study: 7 to 15 years; Sexes eligible for study: both; Accepts healthy volunteers: no; Inclusion criteria: (1) Diagnosis of predominantly spastic unilateral cerebral palsy; (2) Aged 7 to 15 years old at the time of baseline assessment; (3) Sufficient cooperation to comprehend and complete the test and therapy procedures; (4) Minimal ability to actively grasp and hold an object with the more impaired hand (Modified House Functional Classification System ≥ 4); and (5) Having a confirmed impairment in tactile registration and/or tactile perception, as objectified using a clinical assessment battery described under the section ‘eligibility screening’; Exclusion criteria: (1) Botulinum toxin-A injections six months prior to baseline testing; (2) A history of upper limb surgery one year prior to baseline testing; and (3) Inability to communicate in Dutch Study type: Type of study: Interventional; Allocation: randomized; Interventional model: parallel assignment; Masking: single blind (assessor); Primary purpose: clinical intervention; Phase: II Date of first enrollment: August 2023 (actual) Target sample size: 50 (anticipated) Recruitment status: Started on August 8, 2023 Primary outcome(s): Outcome name: Bimanual performance; Method of measurement: Assisting Hand Assessment (AHA); Timepoint: 6 months after the therapy has ended (follow-up) Key secondary outcomes: • Outcome name: Bimanual performance; Method of measurement: Assisting Hand Assessment (AHA); Timepoint: immediately after therapy has ended (post-intervention) • Outcome name: Bimanual performance; Method of measurement: Children’s Hand-use Experience Questionnaire (CHEQ); Timepoint: immediately after therapy has ended (post-intervention) and 6 months after the therapy has ended (follow-up) • Outcome name: Bimanual coordination; Method of measurement: Box opening task; Timepoint: immediately after therapy has ended (post-intervention) and 6 months after the therapy has ended (follow-up) • Outcome name: Bimanual coordination; Method of measurement: Kinarm Exoskeleton (‘Ball-on-bar task’); Timepoint: immediately after therapy has ended (post-intervention) and 6 months after the therapy has ended (follow-up) • Outcome name: Tactile registration; Method of measurement: Semmes–Weinstein Monofilaments; Timepoint: immediately after therapy has ended (post-intervention) and 6 months after the therapy has ended (follow-up) • Outcome name: Tactile perception; Method of measurement: Stereognosis, Aesthesiometer, Tactile Discrimination Test; Timepoint: immediately after therapy has ended (post-intervention) and 6 months after the therapy has ended (follow-up) • Outcome name: Proprioception; Method of measurement: Kinarm Exoskeleton (‘Contralateral position matching task’, ‘Perceptual boundary task’, ‘Indicating location task’), ETH MIKE (‘Passive position sense task’), Clinical assessment of movement sense; Timepoint: immediately after therapy has ended (post-intervention) and 6 months after the therapy has ended (follow-up) • Outcome name: Unimanual motor function; Method of measurement: Tyneside Pegboard Test; Timepoint: immediately after therapy has ended (post-intervention) and 6 months after the therapy has ended (follow-up) • Outcome name: Self-perceived occupational performance and goal attainment; Method of measurement: Canadian Occupational Performance Measure (COPM), Goal Attainment Scaling (GAS); Timepoint: immediately after therapy has ended (post-intervention) and 6 months after the therapy has ended (follow-up)

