## Objectives {7}

Therefore, this study protocol describes the design of an RCT comparing the efficacy of Sense for Kids therapy and dose-matched motor therapy to improve sensorimotor upper limb function in children and adolescents with uCP, who present with tactile impairments in the more impaired upper limb. The primary objective is to investigate if somatosensory discrimination therapy results in better bimanual performance at 6 months follow-up, compared to upper limb motor therapy. Secondly, we will investigate if somatosensory discrimination therapy is superior to improve somatosensory impairments. Lastly, we will explore the potential role of behavioral and neurological predictors of therapy response. The results of this study may aid in the selection of the most effective therapy intervention, specifically for children and adolescents with uCP who present with tactile impairments in the upper limb.

We hypothesize that somatosensory discrimination therapy will result in equal improvements in bimanual performance compared to upper limb motor therapy, immediately after the intervention period. However, we expect further improvements in bimanual performance during the follow-up period for participants who received somatosensory discrimination therapy because of the improved upper limb use in daily life, but not after upper limb motor therapy. We further hypothesize larger improvements in proprioceptive function and tactile perception, both immediately after the intervention and at follow-up, in participants who received somatosensory discrimination therapy. By considering the content and organization of the somatosensory discrimination therapy, we expect a higher therapy response for children and adolescents with worse somatosensory function and better attentional functioning at baseline. Lastly, we hypothesize that the occurrence of thalamic lesions is an important predictor of therapy response, because of the crucial role this brain structure has in the processing of somatosensory information that is transmitted from the periphery to the cortex [52].

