##### Secondary outcome measures

**Somatosensory function**

Clinical assessments

Somatosensory function will be measured clinically at all timepoints. These assessments comprise standardized measures for tactile registration, tactile perception, and proprioception. In all clinical assessments, except for the one of stereognosis, the less impaired upper limb is assessed first followed by the more impaired upper limb. To determine threshold values for tactile registration, the Semmes–Weinstein Monofilaments will be used. This test consists of a kit of 20 nylon monofilaments (Jamar® Monofilaments, Sammons Preston, Rolyan, Bolingbrook, IL, United States) [12, 75]. The score is the lowest filament at which the participant was able to correctly identify three consecutive touches. The assessment starts with the monofilament that represents the lower border of normal tactile registration (0.07 g). Afterwards, difficulty is increased (i.e., lower filament) or decreased (i.e., higher filament) depending on the performance. Tactile registration will be classified as normal (0.008–0.07 g), diminished light touch (0.16–0.4 g), diminished protective sensation (0.6–2 g), and loss of protective sensation (4.19–300 g). Next, three different components of tactile perception will be assessed: (1) stereognosis or tactile object recognition, (2) two-point discrimination, and (3) texture discrimination. First, stereognosis will be assessed through the tactile identification of familiar objects. This assessment will be performed as described by Klingels et al. [76]. Participants are asked to identify six out of twelve randomly selected objects, of which three are matched in pairs similar in size and shape (pencil/pen, coins/button, paperclip/safety pin) and three clearly different objects (marble, spoon, comb, ball, clothespin, key). The score is the number of correctly identified objects. Second, two-point discrimination will be evaluated using an Aesthesiometer which is placed longitudinally and perpendicularly on the fingertip of the index, as described by Klingels et al. [76]. The test score is the minimal distance that the participant could still discriminate as two discrete points in five consecutive trials. The assessment starts with a distance of 4 mm that is progressively decreased or increased depending on the participant’s performance. A distance higher than 4 mm is considered impaired [77]. Third, the Tactile Discrimination Test will be used to objectify texture discrimination [78, 79]. During this test, participants are guided to feel several triplets of textures with their index finger and are asked to identify which texture out of each set of three is different. The score is calculated based on the difference in texture that the participant is still able to correctly differentiate. Lastly, passive movement sense of the index finger will be evaluated as a measure of proprioception. During this assessment, the metacarpophalangeal joint of the index finger is moved over a small amplitude by the assessor and the participant is asked to indicate if the movement was perceived. If the movement was not perceived, the same procedure is repeated with a larger movement amplitude. Movement sense will be classified as normal (score 2—small amplitude perceived in all three attempts), impaired (score 1—only larger amplitude perceived), or absent (score 0—no movement perceived) [76].

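### Tactile registration has three competing codings (5 categories, 4 classes, filament threshold), and analysing the classes, as Table 1 states, discards resolution the test already records

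*Protocol article*

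**What the plan says.** Three statements in the protocol article describe how tactile registration is scored.

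- Table 1 (Outcomes {12}, Secondary outcomes) gives the method of aggregation as "Classification based on threshold values into 5 categories", coded 1 to 5, with change over time as the analysis metric.
- The Somatosensory function section names four classes, with limits in grams: "Tactile registration will be classified as normal (0.008–0.07 g), diminished light touch (0.16–0.4 g), diminished protective sensation (0.6–2 g), and loss of protective sensation (4.19–300". No fifth class appears.
- The same section says of the test: "This test consists of a kit of 20 nylon monofilaments". It then defines the result: "The score is the lowest filament at which the participant was able to correctly identify three consecutive touches".

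The administrative table lists the measure as a key secondary outcome, after therapy and at 6 months: "Outcome name: Tactile registration; Method of measurement: Semmes–Weinstein Monofilaments". It falls under the second aim in Objectives {7}: "Secondly, we will investigate if somatosensory discrimination therapy is superior to improve somatosensory impairments".

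**The concern.** Table 1 is where the article fixes what is analysed, and its coding differs from the one the text defines. The filament threshold is a third candidate. Statistical methods {20a} allows linear or generalized mixed models, so an unsettled scale also leaves the type of model open. That choice could then be made after the data are seen.

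A second issue follows if Table 1 is taken at its word. The threshold is recorded on up to 20 levels and then grouped into a handful of classes before change is computed. Movement inside a class counts as no change. For a trial of 25 children per group, with superiority on somatosensory impairment as its second aim, this makes the outcome less able to show a difference that the test has already measured.

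**Working it through.** **1. The codings side by side.** Table 1 has five categories and the text has four classes. Other ordinal outcomes agree between Table 1 and the text: Goal Attainment Scaling has six levels from −3 to 2 in both, and movement sense has three levels from 0 to 2 in both. The mismatch is therefore specific to this measure. The nearest comparable test, the aesthesiometer, is also a threshold test, and Table 1 keeps it in millimetres.

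**2. Resolution lost, from the documents' own figures.** Widths of the four classes in log10 grams:

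- normal: log10(0.07/0.008) = 0.94
- diminished light touch: log10(0.4/0.16) = 0.40
- diminished protective sensation: log10(2/0.6) = 0.52
- loss of protective sensation: log10(300/4.19) = 1.85

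The full span is log10(300/0.008) = 4.57, so the last class alone takes 1.85/4.57 = 41% of it. If all 20 filaments fall within the four classes, the average is 20/4 = 5 per class. At least one class then holds five or more filaments, and a child can move four filaments inside it with a change of zero. With five classes sharing the filaments the average is 4, and the same argument gives three filaments.

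**3. The plan's own sample size.** The article states no power for tactile registration. Its only calculation is for the Assisting Hand Assessment: effect size 0.9, two-sided alpha 0.05, power 0.80. A noncentral t calculation gives 21 per group (power 0.812), as the article states. That figure does not depend on this point.

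**4. Effect on power, under assumptions.** The documents give no mean, SD, visit-to-visit variability or expected effect for the monofilaments, nor the number of filaments per class. The simulation assumed:

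- 21 children per group
- between-child SD of 3 filament steps
- within-child visit SD of 1, 1.5 or 2
- mean baseline rank of 5, 8 or 12
- filaments per class of 4/2/4/10 or 5/5/5/5
- baseline-adjusted comparison, two-sided 0.05, no multiplicity correction

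In each of the 18 scenarios (2 splits × 3 means × 3 SDs) the effect was set to give about 80% power on the 20-level score; this took 1.29 to 2.52 filament steps. The same data were then regrouped. The five-class version split off the top filament (first split) or used five bands of four (second split). Selected results, including the extremes:

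| Split | Mean rank | Visit SD | 20 levels | 4 classes | 5 classes |
|---|---|---|---|---|---|
| 4/2/4/10 | 5 | 1 | 0.807 | 0.508 | 0.508 |
| 4/2/4/10 | 8 | 2 | 0.800 | 0.686 | 0.687 |
| 4/2/4/10 | 12 | 1 | 0.797 | 0.350 | 0.358 |
| 5/5/5/5 | 5 | 1 | 0.802 | 0.344 | 0.430 |
| 5/5/5/5 | 12 | 2 | 0.799 | 0.652 | 0.700 |

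With four classes the loss runs from 0.800 − 0.686 = 11 points to 0.802 − 0.344 = 46 points. With five it runs from 0.799 − 0.700 = 10 points to 0.797 − 0.358 = 44 points. Power fell in all 18 scenarios.

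**5. A second set-up.** This used a t-test on change, the 4/2/4/10 split, between-child SD 3 and a gain of 1.5 filament steps over control.

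- 25 per group, visit SD 1.2, baseline mean 5.5: 79% on filament level, 52% on four classes.
- Same, baseline mean 12: 84% and 45%.
- Baseline mean 5.5, visit SD 2: 39% and 28%.
- Baseline mean 5.5, visit SD 1.2, 21 per group: 72% and 45%.

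The direction is the same throughout. With noisier visits the gap narrows, and neither coding has adequate power.

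**The case against.** A reader might infer that either Table 1 or the text must be wrong. The documents do not establish that. The four classes end at 300 g and give no code to a child who feels no filament; a fifth code for that case would reconcile the two, and the full protocol may define one. The article does not say so. What stands is that its two statements differ and need reconciling.

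A reader might also infer that both places throw the threshold away. They do not. The text defines the score as the lowest filament identified before it gives the classes; only Table 1 names the classes alone as the aggregation. The threshold is recorded, so nothing is lost at data collection.

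Nor are the power figures a measured loss. Every input is assumed, and the size changes several-fold with them. They also use an unadjusted 0.05, whereas the plan applies mixed models and false discovery rate control to secondary outcomes.

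Classes are a legitimate choice. Eligibility requires impaired registration and/or perception, so a child may enter with normal registration. Under the second set-up with baseline mean 5.5, about 38% start in the normal class, and a filament-level analysis counts their movement as benefit. Whether it should is a question of clinical meaning. This is a real cost of the change.

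Finally, the importance is limited. The directional hypotheses name proprioception and tactile perception, the therapy components are object recognition, texture discrimination and body position sense, and Table 1 holds several other somatosensory measures.

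**Conclusion.** The point holds as a problem of outcome definition with a cost in sensitivity. The article gives three codings for one listed secondary outcome and does not say which is analysed. If the classes are used, as Table 1 states, recorded resolution is lost. That follows from the article's own figures, since one class covers 41% of the log-force range.

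The power loss is consistent in direction, at about 10 to 46 percentage points in scenarios calibrated to roughly 80% power on the full scale. That range rests wholly on assumed baseline level, visit noise and band widths and should not be quoted as a property of this trial.

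It would be an over-reading to treat this as a threat to the trial's main conclusion: the primary outcome, its analysis and the sample size of 21 raised to 25 per group do not depend on it. It is worth correcting because the remedy costs little and should be fixed before the outcome data are examined.

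**What to change.** In Table 1, name the recorded threshold as the analysed variable, either filament rank or log10 force in grams, in a linear or ordinal mixed model. State in advance the code for a child who feels no filament. Report the clinical classes descriptively by group and timepoint, and make their number and definitions the same in Table 1 and in the Somatosensory function section, including whether a fifth code exists.

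The cost is a change of wording in Table 1, the text and the analysis plan, through the amendment route the article already describes. No extra testing is needed, because the threshold is already the score taken. There are two downsides: the main result is less familiar to clinicians than the class labels, and some movement within the normal range will count as change. The descriptive class table makes the latter visible.

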
Kinarm Exoskeleton: Contralateral position matching task, Perceptual boundary task and Indicating location task

Proprioception of the shoulder and elbow joints will be assessed simultaneously using the Kinarm Exoskeleton robotic device (Kinarm, BKIN Technologies Ltd, Kingston, Canada). Participants are seated on a height-adjustable chair with both upper limbs positioned in individually calibrated arm supports, allowing for upper limb movements in the horizontal plane. A virtual reality screen is positioned above the upper limbs to display task visuals and to occlude direct vision of the upper limbs. To objectify proprioception, three different tasks will be performed: (1) the contralateral position matching task, (2) the perceptual boundary task, and (3) the indicating location task. All tasks are first performed with the less impaired upper limb, followed by the more impaired upper limb. First, the contralateral position matching task is a valid measure of static position sense during which the robot passively moves the upper limb that is being assessed to one out of four spatial targets, each separated by 12 cm [80, 81]. Afterwards, the participant is instructed to actively mirror-match this position with the contralateral upper limb. Each participant performs 24 trials, resulting in four parameters describing position sense (i.e., absolute error, variability, contraction/expansion and systematic shift). The second task, the perceptual boundary task, is an adapted version of the task described by Vandevoorde et al. [82]. During this task, a passive upper limb reaching movement with an angular deviation relative to a straight line is performed by the robotic device. The robot then passively returns the upper limb to the starting position. Afterwards, participants are asked to indicate whether the performed movement deviated to the left or right compared to a straight line. The angular deviation applied on the next trial depends on the performance and is determined via a parameter estimation by sequential testing procedure, in order to estimate how accurately each participant can discriminate angular deviations. A more detailed description of the procedure to calculate the final parameter can be found elsewhere [82]. Some minor adaptations compared to the protocol described by Vandevoorde et al. were made to increase applicability in children and adolescents with uCP. Colored symbols were added on the left and right side of the virtual screen to assist in describing the direction of the deviation (i.e., left/yellow duck and right/green car). Next, a straight reference line was added on the screen to improve task comprehension. Lastly, the movement was made passive to avoid interference of motor impairments that might be present in the upper limb. In the third proprioceptive task (indicating location task), the robot passively moves the upper limb to one out of four prespecified locations. The participant is then asked to indicate the perceived position of the tip of their index finger. Each potential location is marked by a colored circle containing a white figure to assist in describing the location (i.e., apple/green, tree/red, flower/yellow, house/blue), with at least 5 cm of distance between neighboring locations. Each participant will perform a total of 12 trials. The final score is the number of trials during which the participant correctly identified the location of the hand. The three tasks will be performed at all timepoints.

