##### Motor function

Children’s Hand-use Experience Questionnaire

The Children’s Hand-use Experience Questionnaire (CHEQ) is an online questionnaire that captures the child’s experience of using the more impaired hand during 29 daily bimanual activities (available online at: http://www.cheq.se/questionnaire) [86]. This questionnaire will be completed by the parents or legal caregiver. For each bimanual activity, the parents are asked to indicate if the child or adolescent uses one or both hands to perform the activity or if assistance is needed. Followed by three sub-questions that are scored on a 4-point Likert scale, indicating the (1) efficacy of the more impaired hand, (2) time needed to perform the activity compared to peers, and (3) if the child feels bothered by the more impaired hand when performing the activity. The CHEQ has shown to be reliable and valid for the use in children and adolescents with uCP [87]. This questionnaire will be completed at each timepoint.

Kinarm Exoskeleton: Ball-on-bar task

The standardized ball-on-bar task will be performed on the Kinarm Exoskeleton to quantify bimanual coordination. The fingertips of the participant are connected using a virtual bar of 20 cm on which a ball is positioned. The participants are instructed to move the ball to circular targets, while keeping it balanced on the bar. The task has two difficulty levels; in the first level, the ball is fixed to the bar, while in the second level, the ball moves when the bar is being tilted. A more detailed description of the set-up and task can be found elsewhere [81, 88]. Parameters of interest are determined based on previous research in children and adolescents with uCP [89] and include bar tilt standard deviation, hand path length bias, reaction time difference, and hand speed difference. This task will be performed at every timepoint.

Box opening task

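### Two secondary proprioception parameters, the perceptual-boundary inflection point and contraction/expansion, have their best value between two directions, so change over time in them does not measure improvement

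*Protocol article*

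**What the plan says.** In Outcomes {12}, Table 1, the secondary outcomes carry the analysis metric "Change over time". It is entered once at the top of the block, and the blank cells below it read as applying to every row. The perceptual boundary task is summarised as "Slope and inflection point of the psychometric curve" and the contralateral position matching task as "Mean scores across 24 trials".

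The Kinarm section describes the boundary task: "participants are asked to indicate whether the performed movement deviated to the left or right compared to a straight line". For position matching it names "four parameters describing position sense (i.e., absolute error, variability, contraction/expansion and systematic shift". It refers the reader to a cited paper for how the boundary-task parameter is computed: "A more detailed description of the procedure to calculate the final parameter can be found elsewhere".

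Statistical methods {20a} fits mixed models and reads the time-by-group interaction as a difference between arms in improvement. Its only transformation rule is for data that are not normally distributed. Objectives {7} states the hypothesis these outcomes serve: "We further hypothesize larger improvements in proprioceptive function and tactile perception".

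**The concern.** A between-arm comparison of mean change measures improvement only if better always means movement in the same direction along the scale. That is not so for the inflection point of a left/right judgement, which is the deviation that the child feels as straight. A child who goes from 6 degrees left to 0 and a child who goes from 6 degrees right to 0 have both improved fully. With right coded as positive, their changes are +6 and -6, and the mean is 0.

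Contraction/expansion has the same structure. Contracted and expanded workspaces are both errors, and the ideal lies between them.

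Two errors can follow. A therapy that truly reduces bias may show no between-arm difference. Conversely, an arm whose average bias drifts to one side may show a significant difference although accuracy has not improved. Both bear on the proprioception hypothesis.

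**Working it through.** **Step 1. Which parameters have two wrong directions?**

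| Parameter | Direction of improvement, from the article |
|---|---|
| Boundary task: slope | One direction |
| Boundary task: inflection point | Two directions, ideal at zero (left/right judgement) |
| Position matching: absolute error, variability | Lower is better |
| Position matching: contraction/expansion | Two directions, ideal in between |
| Position matching: systematic shift | Sign convention not stated |
| Movement sense (0–2), indicating location (0–12) | Higher is better |
| ETH MIKE mean absolute error | Lower is better |
| Ball-on-bar: bar tilt standard deviation | Lower is better |
| Ball-on-bar: hand path length bias, reaction time difference, hand speed difference | Sign convention not stated |

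The article's wording establishes the problem for two parameters. A transformation triggered by non-normality would not correct it, because a signed bias can be perfectly normal.

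**Step 2. Size of the cancellation (illustration).** The plan gives no figure for these parameters, so there is none to reproduce. Its 21 per group for the primary outcome does reproduce (exact two-sided t-test, effect size 0.9: power 0.792 at 20 and 0.812 at 21 per group) and is not in dispute. From the plan I take only 25 per group and two-sided alpha 0.05. Everything else is assumed: size of bias with mean 6 and SD 2 degrees, measurement error SD 2 at each visit, bias halved in one arm and unchanged in the other, and a fraction p of children erring in the same direction.

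Expected signed difference = -(2p - 1) × 0.5 × 6 = -3(2p - 1). At p = 0.5 this is 0, at p = 0.7 it is -1.2, and at p = 1 it is -3. Simulation (10,000 runs per setting, two-sample t-test on change) gives:

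| p | Signed difference | Power, signed | Power, absolute |
|---|---|---|---|
| 0.5 | 0.01 | 0.05 | 0.94 |
| 0.6 | -0.61 | 0.10 | 0.94 |
| 0.7 | -1.20 | 0.23 | 0.94 |
| 0.8 | -1.82 | 0.47 | 0.94 |
| 0.9 | -2.41 | 0.74 | 0.94 |
| 1.0 | -3.01 | 0.95 | 0.94 |

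The absolute difference is about -2.85 in every row.

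**Step 3. A second set of assumptions.** True bias normal with SD 1, one arm's bias halved, 25 per arm. With mean bias 0, signed power is about 5%. Absolute power is about 92% with error SD 0.25 and about 43% with error SD 0.5. With mean bias 0.5 SD, signed power is 41% and 19%, against 97% and 53%.

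**Step 4. The opposite error.** On the Step 3 scale, let one arm's bias start symmetric about zero and drift by 0.5, with the other arm unchanged. The SD of change is √2 × error SD.
- Error SD 0.25: 0.5/0.354 = 1.414; noncentrality 1.414 × √(25/2) = 5.0; the signed test is significant in over 99% of trials.
- Error SD 0.5: 0.5/0.707 = 0.707; noncentrality 2.5; significant in 69%.

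Meanwhile the mean true absolute bias in that arm gets worse, from √(2/π) = 0.80 to 0.7979 × e^(-0.125) + 0.5 × 0.3829 = 0.90.

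**The case against.** The strongest reply is that change over time is a generic label. The article nowhere says raw or signed, and it leaves scoring to cited papers and the full protocol. A sign convention, or recoding to the more impaired side, may be set there.

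This stands for part of the list. A reader might infer that the coordination outcomes are affected too, since the ball-on-bar parameters are "bar tilt standard deviation, hand path length bias, reaction time difference, and hand speed difference". Three of these names suggest an ideal at zero, as does systematic shift in the matching task. But the article does not say whether they are signed or absolute, so it does not support that inference.

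The reply does not remove the point for the other two. However it is estimated, the inflection point of a left/right curve is a location on a left/right axis, and contraction/expansion names two opposite errors. Table 1 does specify an absolute error for ETH MIKE and puts no such qualifier on the inflection point. Recoding to the more impaired side would align directions anatomically, but would still leave zero as the best value.

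A reader might also infer that the proprioception hypothesis cannot be tested, or that cancellation is certain. Neither follows. Slope, absolute error, variability, movement sense, indicating location and ETH MIKE error all still test the hypothesis. The loss also disappears when all children err in the same direction, and the documents do not say how mixed the directions will be.

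**Conclusion.** The point holds for two secondary parameters: the inflection point and contraction/expansion. As written, their time-by-group test does not measure improvement. The loss of power ranges from complete, with evenly mixed directions, to none, when all children err alike. Mixing is plausible because responses are left or right and the article states no recoding by affected side, but it is not documented. All power figures are illustrations on assumed inputs and say nothing about what this trial will observe.

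The primary outcome and sample size are untouched. Severity is minor.

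**What to change.** In Table 1:
- Define the inflection-point outcome as the absolute value in degrees from straight, and the contraction/expansion outcome as the absolute deviation from its no-distortion value on the scale used. State that lower is better for both.
- Report the signed values, coded relative to the more impaired side, as supplementary.
- For systematic shift, hand path length bias, reaction time difference and hand speed difference, state whether they are signed, and apply the same rule only if they are.
- Leave slope, absolute error and variability as they are.

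The cost is a wording change and one recoding step. No new data are needed, because the more impaired side is already recorded at baseline. Making the change before unblinded data are analysed also rules out a later choice between signed and absolute versions.

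There are two downsides. Absolute values are skewed, which the transformations or generalized models already allowed in Statistical methods {20a} can handle. They also rise with measurement noise: with the error SD of 2 assumed above, a child with no true bias has an expected absolute value of 2 × 0.798 = 1.6. A change in precision alone can therefore move them, so they should be read alongside slope or variability.
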